#### Study End Points

The primary feasibility end point will be determined by the number of times each participant completes the eCARE assessment out of a total of 6 possible time points over an 8-week period. Participants who complete the assessment at least 4 times (≥ 66.6% completion rate) will be considered to have met the feasibility threshold. The feasibility study will be deemed successful if at least 60% of enrolled participants (n≥36) reach this threshold. The secondary acceptability end point will be assessed using the AIM, a psychometrically validated implementation science instrument designed to evaluate participants’ perceptions of intervention acceptability. An average AIM score of 4 out of 5 will be interpreted as indicative of acceptable intervention uptake.

### Measures

As part of this study, we are collecting a comprehensive set of variables to capture the multifaceted experiences of caregiving.

#### Sociodemographic Characteristics

Sociodemographic characteristics include participants’ age, sex, gender identity, race and ethnicity, educational attainment, relationship status, employment status, insurance coverage, and household income.

#### Clinical Characteristics (Care Recipient)

Clinical characteristics of the care recipient—such as their age, sex, cancer diagnosis, cancer stage, and type of treatment—are recorded to contextualize the caregiving experience.

#### Caregiving Characteristics

To further understand the caregiving context, we will gather data on the length of the caregiving period, the caregiver’s relationship to the care recipient, primary caregiver status, and cohabitation. We will also assess caregiving intensity through the number of hours of care provided per week, the types of tasks performed, and the care recipient’s level of independence in activities of daily living, measured by the Katz Index [84].

### Outcome Measures

#### Psychological Distress

Depression is measured by the PHQ-9*,* a validated, self-administered instrument widely used to screen for, diagnose, and monitor the severity of depressive symptoms [64]. Respondents rate the frequency with which they have experienced each symptom over the past 2 weeks on a 4-point Likert scale, ranging from 0 (“Not at all”) to 3 (“Nearly every day”), yielding a total score between 0 and 27. Interpretation of PHQ-9 scores follows standard clinical guidelines: 0-4 (minimal depression), 5-9 (mild), 10-14 (moderate), 15-19 (moderately severe), and 20-27 (severe). A total score of 10 or higher is commonly used as a cutoff for identifying clinically significant depressive symptoms. Item 9 specifically assesses suicidal ideation and requires immediate clinical attention if endorsed. The PHQ-9 has demonstrated strong reliability and construct validity across diverse populations and care settings, including oncology. The excellent psychometric property of the PHQ-9 has been reported across different age and racial or ethnic groups, endorsing its utility among patients with cancer [85]. The GAD-7 is a widely used, self-administered instrument designed to assess the severity of generalized anxiety symptoms over the past 2 weeks. It includes 7 items corresponding to core symptoms of generalized anxiety disorder. Each item is rated on a 4-point Likert scale ranging from 0 (“Not at all”) to 3 (“Nearly every day”), yielding a total score between 0 and 21 [65]. Interpretation of total scores follows established clinical cut points: 0-4 (minimal anxiety), 5-9 (mild), 10-14 (moderate), and 15-21 (severe). A score of 10 or above is commonly used as a threshold for identifying clinically significant anxiety symptoms, warranting further assessment. The GAD-7 demonstrated excellent internal consistency (α=.92), strong test-retest reliability, good criterion, construct, and convergent validity [65,86]. These strong psychometric properties have been confirmed across age groups and racial and ethnic backgrounds, including those diagnosed with cancer [87-89].

#### Closeness

The Inclusion of Other in the Self (IOS) Scale [68,90] is a widely used, single-item pictorial measure of interpersonal closeness. Grounded in self-expansion theory [91,92], the IOS assesses the degree to which individuals perceive their relationship partner as integrated into their sense of self. In the current study, the IOS was used to evaluate perceived emotional closeness between family cancer caregivers and their care recipients. Participants are shown seven pairs of circles labeled “Self” and “Other,” ranging from no overlap (1) to almost complete overlap (7). They are asked to select the pair that best represents their relationship with the care recipient. This visual analog approach provides a rapid and intuitive assessment of relational closeness and has demonstrated validity across diverse populations [69,91,93,94]. The IOS has been linked to a variety of relationship and health outcomes and is commonly used in studies of romantic, familial, and community ties [92]. In this study, caregiver-reported IOS scores provide a snapshot of the emotional bond between caregiver and care recipient, an interpersonal factor that may influence psychological distress, motivation to engage in support tools, and the caregiving experience more broadly.

#### Caregiving Burden

Caregiving burden is assessed with the Zarit Burden Interview-Short Form (ZBI-12) a 12-item self-report measure used to assess the subjective burden experienced by informal caregivers [67]. It evaluates key dimensions of caregiver strain, including emotional, physical, and social impacts associated with caregiving responsibilities. Each item is rated on a 5-point Likert scale ranging from 0 (“Never”) to 4 (“Nearly always”), yielding a total score ranging from 0 to 48, with higher scores indicating greater perceived burden. Standard scoring guidelines categorize burden levels as follows: 0-10 (no to mild burden); 10-20 (mild to moderate burden); >20 (high burden). The ZBI-12 has demonstrated strong reliability and validity across diverse caregiving populations, including those caring for individuals with dementia, cancer, and other serious illnesses.

#### Communication

The Social Constraints Scale (SCS) is a 15-item self-report instrument developed to assess the extent to which individuals perceive their social environment, particularly close others such as spouses or family members, as inhibiting or discouraging the expression of illness-related thoughts and emotions [70,71]. In the context of cancer, the SCS captures perceived social responses that constrain open communication, such as minimizing concerns, changing the subject, or expressing discomfort when the patient discusses their cancer-related experiences. Each item is rated on a 4-point Likert scale ranging from 1 (“Never”) to 4 (“Often”), with higher total scores (ranging from 15 to 60), indicating greater perceived social constraint. The SCS has demonstrated strong psychometric properties across diverse populations coping with chronic illness.

#### Perceived Responsiveness

Caregivers’ perceptions of care recipient responsiveness were measured by the 12-item Perceived Partner Responsiveness Scale (PPRS) [72]. The PPRS measures the degree to which people feel their loved ones are responsive to them. It measures two dimensions of perceived responsiveness in close relationships: (1) understanding (7 items, eg, “My loved one gets the facts right about me;” “My loved one knows me well”) and (2) validation (5 items, eg, “My loved one values and respects the whole package that is the real me;” “My loved one seems interested in what I am thinking and feeling”). Responses were scored on a 9-point Likert scale ranging from 1 (not at all true) to 9 (completely true). A total score is calculated by summing all items [72], with scores indicating greater perceptions of others’ responsiveness.

#### Communal Motivation to Care

Communal motivation was assessed with the 10-item Partner-Specific Communal Motivation Scale [74]. Caregivers were asked to assess to what extent they were communally motivated to care for the well-being of their care recipients. Responses were scored on a 9-point Likert scale ranging from 1 (not at all) to 9 (extremely). Example items are “Helping my loved one is a high priority for me,” “I would sacrifice very much to help my loved one,” “I would be reluctant to sacrifice for my loved one*.*” The total score is given by the sum of the items after reversing items 2, 5, and 10, and indicates higher levels of communal motivation.

#### Quality of Life

The Centers for Disease Control and Prevention (CDC) healthy days measure, commonly referred to as health-related quality of life-4 (HRQOL-4), is a brief, validated instrument designed to assess health-related quality of life in population-based studies and public health surveillance [66]. The HRQOL-4 includes 4 core items, including self-rated general health, physically unhealthy days, mentally unhealthy days, and physical or mental health interference with daily activities. Each item captures a distinct domain of the HRQOL-4, allowing for both individual and composite assessments of overall well-being. The HRQOL-4 has demonstrated strong reliability and validity across diverse populations [66,95].

#### Acceptability of Intervention

The AIM is a pragmatic, 4-item self-report instrument developed to assess stakeholders’ perceptions of the acceptability of a specific intervention or implementation strategy [76]. The AIM captures the extent to which an intervention is perceived as agreeable, satisfactory, or palatable, with items rated on a 5-point Likert scale ranging from “completely disagree” to “completely agree.” The items include (1) “(Intervention) meets my approval,” (2) “(Intervention) is appealing to me,” (3) “I like (Intervention),” and (4) “I welcome (Intervention).” It has been designed for use across diverse stakeholder groups, including service providers, administrators, and caregivers, and it requires no specialized training for administration or interpretation. While no established cutoff scores exist, higher total scores indicate greater acceptability. The AIM has demonstrated strong psychometric properties, including content and structural validity, reliability, and responsiveness to change [76].

#### User Engagement

The User Engagement Scale (UES-SF) is a 12-item self-report instrument developed to assess user engagement in human-computer interaction contexts [77]. The short form includes four key subscales, each with 3 items: focused attention, perceived usability, aesthetic appeal, and reward*.* Participants respond using a 5-point Likert scale ranging from 1 (“Strongly Disagree”) to 5 (“Strongly Agree”). Per scoring instructions, items within the perceived usability subscale are reverse coded. Subscale scores are computed by averaging the responses within each domain, and a total engagement score is calculated by averaging across all 12 items. The UES-SF was designed for high usability, with items written at a fifth-grade reading level and no special training required for administration or interpretation. The instrument has demonstrated sound psychometric properties, including content and structural validity, internal consistency, and responsiveness to user experiences [77].

### Data Analysis

Quantitative and qualitative data will be analyzed using a mixed methods approach to evaluate the feasibility and acceptability of the eCARE tool among family caregivers of individuals diagnosed with cancer. Descriptive statistics will be used to summarize participants’ sociodemographic, clinical, and caregiving characteristics, including means, SDs, ranges, and 95% CIs. Graphical methods (eg, histograms, boxplots, and scatterplots) will be used to examine variable distributions and identify the need for transformations. For comparisons, we will use ANOVA for continuous variables and chi-square tests for categorical variables. Differences in psychological distress, caregiving burden, relational closeness, perceived responsiveness, and motivation to provide care will also be explored. Feasibility, the primary outcome of Aim 1, will be assessed based on the number of participants completing at least 4 of 6 total weekly eCARE assessments during the 8-week study period. Participants exceeding 6 sessions due to more frequent use will be classified as having met the feasibility threshold, consistent with those completing at least 4 of 6 sessions. The study will be considered feasible if 60% or more of enrolled participants (≥36 of 60) achieve this end point. Acceptability, the secondary outcome, will be assessed using the AIM [76]. The mean and SD of AIM scores will be calculated, with an average score of ≥4.0 (on a 5-point scale) interpreted as evidence of acceptability. Exploratory latent growth curve modeling will be used to examine changes in depression and anxiety symptoms over time (measured by PHQ-9 and GAD-7). These analyses are considered exploratory due to the limited statistical power associated with the sample size (n=60).

For Aim 2, qualitative data from semi-structured interviews with a purposive subsample of 20 family caregivers (including both completers and noncompleters) will be analyzed using thematic content analysis in ATLAS.ti [96]. Interview transcripts will be transcribed verbatim and independently coded by trained research staff. An initial coding scheme will be developed inductively and applied iteratively. Two independent coders will review all transcripts, with discrepancies resolved through discussion until consensus is achieved [97]. Axial coding and thematic mapping will be used to identify higher-order categories related to eCARE’s perceived strengths and limitations, usability, relevance, and reported facilitators or barriers to engagement. Analysis will continue until thematic saturation is reached, defined as the point at which no new codes or themes emerge [79,97,98].

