**Methods:**

In Phase 1, a total of 60 United States–based family caregivers will be recruited from community health clinics, cancer and caregiving advocacy groups, and online postings. Screened and enrolled caregivers will complete 6 eCARE sessions over an 8-week period. Pre- and posttest surveys assess depression, anxiety, caregiving burden, and relational processes. Feasibility will be evaluated based on the proportion of participants who complete at least 66% of weekly assessments, and acceptability will be assessed using the acceptability of intervention measure (AIM). In Phase 2, a total of 20 caregivers will be invited to participate in semi-structured online interviews to explore user experience, including perceived benefits, barriers to use, and preferences for future implementation. Qualitative data will be analyzed thematically to inform tool refinement.

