
#### Enrollment and Participation

Interested individuals who meet initial eligibility criteria will be contacted by study staff to schedule an initial phone screening, after which informed consent will be obtained and baseline measures collected through a pretest electronic survey. Participants will be asked to use the eCARE app weekly for 6 sessions (T1-T6) over an 8-week period. Weekly phone-based reminders will prompt engagement with the platform. If an assessment is missed, the app will automatically issue 2 follow-up notifications within 24-48 hours. Platform usage data will be collected to assess adherence (eg, frequency and duration of app use). A brief posttest assessment (T7) will be conducted approximately 8 weeks after baseline; the survey will include the same instruments presented during the pretest assessment plus the acceptability (AIM questionnaire [76]) and user engagement questionnaires (User-Engagement Scale-Short Form [77]).

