**Primary outcome**			
	Feasibility end point (eCARE^a^ completion rate)	Number of eCARE completions during 8-week period Proportion of participants achieving feasibility end point	≥4 completions (≥66.6%) = end point achieved Study feasible if ≥60% of participants (≥36) reach this threshold

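### The primary feasibility endpoint is framed as 4 of 6 weekly assessments, but anyone with more than 6 sessions passes whatever the spacing, and Table 3 scores a plain count

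*Protocol article*

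**What the plan says.** Several sections describe the endpoint in weekly terms. The Methods paragraph of the Abstract bases feasibility on "the proportion of participants who complete at least 66% of weekly assessments". Enrollment and Participation sets the schedule: "Participants will be asked to use the eCARE app weekly for 6 sessions (T1-T6) over an 8-week period". Data Analysis opens its definition with "the number of participants completing at least 4 of 6 total weekly eCARE assessments during the 8-week study period".

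The scoring rules are worded differently. Under Study End Points the endpoint is "determined by the number of times each participant completes the eCARE assessment out of a total of 6 possible time points over an 8-week period", and the participant-level rule is: "Participants who complete the assessment at least 4 times (≥ 66.6% completion rate) will be considered to have met the feasibility threshold". Table 3 defines the primary outcome as "Number of eCARE completions during 8-week period", with a pass at four or more and no reference to weeks or scheduled assessments. Data Analysis, straight after its weekly definition, adds: "Participants exceeding 6 sessions due to more frequent use will be classified as having met the feasibility threshold".

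The study is declared feasible if at least 60% of those enrolled, 36 of 60, pass. This is a cut on the observed number, with no margin around it.

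**The concern.** Completing weekly assessments and completing a number of sessions are different quantities once a participant can record more than once a week. Data Analysis expects that to happen, since it provides for users who go beyond six sessions because they use the app more often. Study End Points, by contrast, allows six opportunities and no more.

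The sentence on heavy users decides who passes the primary endpoint, so it cannot be put down to detail that a journal article leaves out. It credits a burst of use in the same way as adherence to the weekly schedule. The Discussion says the findings will inform a larger randomized trial. That trial's planners need to know whether caregivers keep to repeated weekly monitoring, and a positive result under this rule would not necessarily show it.

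**Working it through.** **Reproducing the stated cuts.** Inputs: 4 of 6 assessments (Study End Points, Data Analysis, Table 3) and 60% of 60 enrolled (the same places). 4/6 = 0.667, which agrees with the stated 66.6% bar. 0.60 × 60 = 36, which agrees with the stated 36. Both thresholds are sound as arithmetic. The problem lies in what is counted towards them.

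**Applying each wording to the same participant.**

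| Pattern of use | Scheduled assessments T1–T6 covered | 4 of 6 scheduled assessments | Table 3 count (4 or more) | Sentence on more than 6 sessions |
|---|---|---|---|---|
| One session in each of four scheduled weeks | 4/6 = 66.7% | pass | pass | not applicable |
| Four sessions in one week, none later | 1/6 = 16.7% | fail | pass | not applicable |
| Seven sessions in one week, none later | 1/6 = 16.7% | fail | pass | pass |
| Seven or more sessions, at least one in every scheduled week | 6/6 = 100% | pass | pass | pass |

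The third row follows from the explicit text on any reading. If the endpoint is a plain count, seven exceeds four. If it is a count of scheduled slots, the added sentence overrides it. The second row depends on the reading: the participant passes under Table 3 taken alone and fails if Study End Points and Data Analysis mean scheduled slots. The last row shows that heavy users who also keep to the schedule lose nothing under a slot rule.

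**Consequence at the cut.** Suppose exactly 36 pass as written and b of them cover fewer than four scheduled assessments. The corrected result is (36 − b)/60:

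- b = 1: 35/60 = 58.3%
- b = 2: 34/60 = 56.7%
- b = 4: 32/60 = 53.3%
- b = 6: 30/60 = 50.0%

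Any b of 1 or more turns a feasible result into a not feasible one.

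**Illustration away from the cut (assumptions, not document figures).** Treat participants as independent, let 50% truly cover four or more scheduled assessments, and let the scoring rule add e percentage points of passers. Then P(X ≥ 36) with X ~ Binomial(60, 0.50 + e) is:

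- e = 0: 0.078
- e = 3 points: 0.169
- e = 5 points: 0.259
- e = 10 points: 0.556

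Nothing in the documents says which e applies.

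**How often heavy users would be misclassified (also an assumption).** If seven sessions fall at random over w weeks, the chance of touching three weeks or fewer is [C(w,1)×1 + C(w,2)×126 + C(w,3)×1806]/w^7, where 1, 126 and 1806 are the numbers of ways seven sessions can fill exactly one, two or three given weeks.

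- w = 8: (8 + 3,528 + 101,136)/2,097,152 = 5.0%
- w = 6: (6 + 1,890 + 36,120)/279,936 = 13.6%

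The same calculation for eight sessions gives 2.0% and 7.1%. Real bursts would be more clustered than random placement.

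**The case against.** The best defence is that the article mostly describes scheduled assessments. It names six time points, Table 1 places app use at T1 to T6 only, and missed assessments trigger app notifications (Enrollment and Participation) and a real-time alert to the team (Participant Safety). Read that way, four recordings in one week would not satisfy 4 of 6, and the bare count in Table 3 is only a short label. This stands for users with 4 to 6 sessions: for them the fault is inconsistent wording. It does not reach users with more than six sessions, whom Data Analysis exempts expressly.

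It can also be said that very frequent use is itself evidence of feasibility, that the Objective speaks of platform completion rates, and that the Limitations already restrict claims about sustained engagement. Volume of use is worth reporting, but it is not a share of weekly assessments, which is how the Abstract and the 66.6% figure present the endpoint. It is also fair that the affected group may be small: under random placement, few users with seven or eight sessions would fall short of four weeks.

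A reader might go further and infer that the 8-week period gives eight weekly chances, so that missed sessions can be caught up later and the real bar is 4/8 = 50% of weeks. The documents do not support this. They fix six time points, treat a missed assessment as a missed slot, and nowhere say that a later session can replace it. Closing times for each slot may stand in the full protocol, so their absence from the article is not a finding.

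**Conclusion.** The point holds for the scoring rule as stated. The automatic pass in Data Analysis conflicts with the six time points in Study End Points and with the weekly definition in the Abstract, in Enrollment and Participation and in Data Analysis itself. It lets clustered use count as weekly adherence. Table 3 adds a second, looser wording of the same endpoint.

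The effect on the trial's result cannot be computed, because the documents give neither the number of participants with more than six sessions nor the timing of sessions. What is certain is that the decision has no margin: with 36 passers, one reclassification changes the conclusion. The probabilities shown above rest on assumed shares and serve only to show sensitivity. This should be fixed, but there is no basis for saying that the feasibility verdict will change, or that the stated 66.6% is the wrong figure.

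**What to change.** Reconcile Study End Points, Data Analysis and Table 3 around one definition:

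- Each scheduled assessment T1 to T6 earns at most one credit, however many sessions are recorded against it.
- A participant meets the endpoint with credit for 4 or more of the 6 scheduled weekly assessments.
- Participants with more than six sessions are scored by the same rule, and the sentence that passes them automatically is deleted.
- Total sessions and duration of use are reported descriptively as engagement data.

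The 4/6 and 36/60 thresholds stay as they are, and no new data collection should be needed. Platform usage data are collected, and the system already flags each missed assessment in real time. The article does not state that session dates are exported, so this should be confirmed. The article puts the start of analysis after the end of data collection, so the rule can be settled and documented before scoring. If scoring has already been done, report the result under both rules. The cost is a few lines of text and possibly a slightly lower feasibility rate.
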